**Rate of early termination = (patients who completed the study early/patients who completed the entire study)∗100**

Analysis of rescue medication use

Independent t-test or Wilcoxon's signed rank test will be conducted to compare the number and dose of use according to different types of rescue medication between the groups.

D. Classification and post hoc analysis of responders and nonresponders

Definition of responders

(1)Those with a minimal CID decrease of NRS 2.5 from the baseline to the date of evaluation. Therefore, responders will be defined as follows. For example, pain reduction of greater than NRS 2.5 will be defined as CID, and CID will be used to divide patients into responders and nonresponders.(2)Using the previously described criteria, patients who had improved symptoms and completed the study early will be considered as responders.

Post hoc analysis

Adequate post-hoc analysis will be conducted by a statistician for differences in treatment results for each treatment group using the responder and non-responder criteria.

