#### Exploratory effectiveness evaluation

2.8.3

1.Additional NBT or surgery for lumbosacral radiculopathy: All patients will be assessed if they underwent any additional NBT or surgical treatment related to lumbosacral radiculopathy on the last day of visit and at 4 weeks after the end of treatment. This assessment will be not conducted on those whose symptoms have improved and ended the study earlier. For patients who dropped out in the middle of the study, the assessment will be performed at 4 weeks after dropout. However, exploratory effectiveness evaluation for dropout participants can be conducted through telephone counseling instead of in-person visits.2.Early termination of treatment: Patients whose symptoms have improved during the study, who request to terminate treatment early, and who no longer require treatment at the discretion of the investigators will be separately evaluated for each group.3.Rescue medication usage: The number of uses, dosage, type, and administration point of rescue medications used between the clinical trial period and final evaluation period will be compared between the 2 groups.

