##### Criteria for early termination

2.8.7.2

1.Patients whose symptoms have improved during the study, who request to terminate early, and who no longer require treatment at the discretion of the investigators can terminate the study earlier than planned.2.Patients who have terminated the study early are not classified as withdrawn/discontinued patients and are considered to have complied with the study treatment.

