The rate of additional treatment will be evaluated by assessing additional NBT or surgery performed for pain control within 4 weeks after the end of treatment. Chi-Squared test or Fisher's exact test will be performed to compare the rate of additional treatment and surgery between the groups.

**Rate of additional procedures = (patients who underwent additional procedures or surgeries/patients who completed the entire study)∗100**

Assessment of treatment early termination rate

Treatment early termination rate will be calculated for each group for patients who satisfied the criteria for early termination of treatment. Chi-Squared test or Fisher exact test will be performed to compare the rate of early termination of treatment between the groups.

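### The two exploratory rates use full-study completers as denominator: early termination may not be a proportion and omits dropouts, and the re-treatment rate omits dropouts who are assessed for it

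*Protocol article*

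**What the plan says.** All references are to the protocol article.

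- **Early-termination rate** (section 2.9, Efficacy evaluation, part C): "Rate of early termination = (patients who completed the study early/patients who completed the entire study", multiplied by 100. The planned comparison is "Chi-Squared test or Fisher exact test will be performed to compare the rate of early termination of treatment between the groups".
- **Additional-procedure rate** (same part): "Rate of additional procedures = (patients who underwent additional procedures or surgeries/patients who completed the entire study", multiplied by 100, and "Chi-Squared test or Fisher's exact test will be performed to compare the rate of additional treatment and surgery between the groups".
- **Who finishes early** (section 2.8.7.2): improved patients who ask to stop and "who no longer require treatment at the discretion of the investigators can terminate the study earlier than planned". The next item adds: "Patients who have terminated the study early are not classified as withdrawn/discontinued patients and are considered to have complied with the study treatment".
- **Who is assessed for re-treatment** (section 2.8.3 and the Table 1 footnote): patients who improved and ended early are not assessed. Dropouts are: "For patients who dropped out in the middle of the study, the assessment will be performed at 4 weeks after dropout".
- **Analysis set** (section 2.9): ITT is the main set for efficacy and per-protocol is secondary. ITT requires randomisation, at least one follow-up and eligibility for efficacy assessment. It does not require completion.

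**The concern.** Both formulas are printed, with their tests, so this is a stated rule and not detail left to another document.

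For early termination, the formula sets finishing early against completing the entire study. Read that way, numerator and denominator have no patients in common, and the result is not a rate. Read more generously, it is a rate among non-dropouts only, although the efficacy section puts ITT first. The dropout rules in section 2.8.7.1 do not bear equally on the arms: the minimum of 6 of 8 acupotomy sessions can remove patients only from the combination arm, while a missed nerve block can remove patients from either. A denominator that shrinks with dropout could therefore differ between arms for reasons unrelated to early improvement.

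For re-treatment, the trial collects the outcome in dropouts and then divides by a group that leaves them out. At stake are two between-arm comparisons that may be read as support for the combination.

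**Working it through.** **Inputs.** From section 2.3: 20 evaluable patients per group and 20% dropout. The plan's figure reproduces: 20 / (1 − 0.20) = 25 per arm, 50 in total. The article gives no expected early-termination, re-treatment or per-arm dropout rates, so those used below are assumptions.

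**Notation, per arm.** E = early finishers, C = patients who stay to the planned end, D = dropouts, and E + C + D = 25. Let p = E/25, the true proportion among all randomised, and d = D/25.

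**Early termination**

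- Narrow reading (early finishers are not completers): E/C = p / (1 − d − p).
- Inclusive reading (early finishers are completers): E/(E + C) = p / (1 − d).

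With d = 0.20:

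| True p | Narrow | Inclusive |
|---|---|---|
| 20% | 0.20/0.60 = 33% | 0.20/0.80 = 25% |
| 40% | 0.40/0.40 = 100% | 0.40/0.80 = 50% |
| 60% | 0.60/0.20 = 300% | 0.60/0.80 = 75% |

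A true difference of 20 points (40% v 20%) prints as 67 points on the narrow reading and 25 points on the inclusive one.

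**Unequal dropout, no true difference.** Take p = 0.30 in both arms and d = 0.28 v 0.08 (assumed).

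- Narrow: 0.30/0.42 = 71% v 0.30/0.62 = 48%.
- Inclusive: 0.30/0.72 = 42% v 0.30/0.92 = 33%.

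In whole patients, with a more extreme split: E = 6 in each arm and D = 9 v 1.

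- Narrow: 6/10 = 60.0% v 6/18 = 33.3%.
- Inclusive: 6/16 = 37.5% v 6/24 = 25.0%.
- All randomised: 6/25 = 24.0% in both.

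The Fisher p-values are 0.24, 0.49 and 1.0, so at this sample size the distortion is in the estimate more than in the significance.

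**The test.** Take E = 8 v 3 and D = 5 in each arm (assumed), so C = 12 v 17.

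| Table used | Rates | Fisher p |
|---|---|---|
| C taken as sample size, E treated as part of it | 66.7% v 17.6% | 0.018 |
| Early v full completers | 8/20 = 40.0% v 3/20 = 15.0% | 0.155 |
| All randomised | 8/25 = 32.0% v 3/25 = 12.0% | 0.171 |

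If E exceeds C, for example 12 early finishers and 8 full completers, the first kind of table needs a cell of 8 − 12 = −4 and cannot be built. The second table is arithmetically sound, but it compares only patients who did not drop out.

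**Re-treatment.** One arm, assumed: 15 full completers, 5 early finishers and 5 dropouts; 3 completers and 3 dropouts are re-treated.

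- Full completers as denominator, dropouts in the numerator only: 6/15 = 40%.
- Full completers as denominator, dropout data discarded: 3/15 = 20%.
- All patients assessed: 6/20 = 30%.
- All randomised, early finishers counted as not re-treated: 6/25 = 24%.

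If early finishers are counted as completers, the denominator holds 5 patients who are not assessed and still omits 5 who are. The mismatch remains.

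Two arms, assumed: C = 12 v 18, D = 5 in each (so E = 8 v 2), re-treated 3 + 3 v 4 + 3 (completers + dropouts).

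- Over full completers: 6/12 = 50.0% v 7/18 = 38.9%.
- Over those assessed: 6/17 = 35.3% v 7/23 = 30.4%.
- Over all randomised: 6/25 = 24.0% v 7/25 = 28.0%.

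The order of the arms changes only in the last line. It does so because early finishers enter the denominator as not re-treated, so the rule for early finishers matters as much as the dropout mismatch. None of these differences is near significance (smallest Fisher p 0.71).

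**The case against.** The strongest reply is that the early-termination denominator may well contain the early finishers. Section 2.8.7.2 says they are not withdrawn and have complied, the Table 1 footnote speaks of them as having completed treatment early, and the per-protocol definition refers to improved patients who met treatment completion criteria. If completers means everyone not withdrawn, the rate is E/(E + C) and cannot pass 100%. This stands: the disjoint reading is the natural one but not certain, so figures such as 100% or 300% hold for that reading only. It does not restore the dropouts, and a formula with two defensible readings and different answers still needs fixing.

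A reader might also infer that the chi-squared and Fisher tests are invalid. The article does not support that. It does not say which table will be tested, and early versus full completers by arm is a valid table. The test breaks only if full completers are used as the sample size. Otherwise the fault is that the comparison is restricted after randomisation.

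A third tempting step is to treat the re-treatment rate as the same error. Early finishers are not assessed for re-treatment, so leaving them out of that denominator agrees with data collection. The direction differs too. Losing more patients inflates the early-termination rate, which flatters an arm. For re-treatment, a smaller denominator with dropouts in the numerator raises the rate, which counts against it.

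Finally, both outcomes are labelled exploratory in a preliminary 50-patient study. That limits the consequence; it does not make the definitions right.

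**Conclusion.** The point holds in limited form. Both denominators conflict with the plan's own choice of ITT as the main efficacy set. At the plan's 20% dropout, the early-termination rate overstates a true 20% as 33% or 25%, and a true 40% as 100% or 50%, depending on whether early finishers count as completers. Under either reading unequal dropout alone can produce a difference between arms. The re-treatment numerator and denominator do not cover the same patients under either reading.

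The formulas and the 20% dropout come from the article. The event rates and the per-arm dropout split are assumed, so the worked figures show what the formulas can do and do not predict this trial's results. The primary ODI analysis and the sample size are untouched. The definitions should be corrected before analysis, at a priority suited to exploratory outcomes.

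**What to change.** In section 2.9, Efficacy evaluation, part C:

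1. **Early termination.** Define the rate as early finishers divided by all randomised (ITT) patients in that arm. Because the article's ITT set requires at least one follow-up, say whether patients without one are in the denominator.
2. **Additional procedures.** Define numerator and denominator over the same patients, with assessed dropouts in both, and state how early finishers are handled, since section 2.8.3 does not assess them. One option is all randomised patients with early finishers counted as not re-treated, plus a sensitivity analysis among those assessed. That option assumes that no early finisher is re-treated, which should be stated.
3. **Tests.** Run the chi-squared or Fisher test on those 2×2 tables and report the difference in proportions with its 95% confidence interval.

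The cost is a few lines of analysis wording and no new data. The early-termination rates will come out smaller than under the present formula.

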**Figure 1 F1:**
[figure not shown]
Study flow chart.

**Table 1 T1:** Clinical trial schedule and observation items.

Period		Screening^∗^ and Baseline	Treatment										Post Treatment	Early termination
Visit	Acupotomy + NBT group	Visit 1	Visit 2	Visit 3	Visit 4	Visit 5	Visit 6	Visit 7	Visit 8	Visit 9	Visit 10	Visit 11	Visit 12	Drop-out
	NBT group	Visit 1			Visit 2		Visit 3			Visit 4		Visit 5	Visit 6	
Day		0	1–3	4–6	7–8	9–11	12–14	15–17	18–20	21–22	23–25	26–28	56–58	
Written consent form		√												
Demographic survey		√												
Medical history, other medical history, and medication administration history		√												
Screening test^†^		√												
Selection/exclusion criteria		√												
Randomization (assignment of registration number)		√												
Physical examination and evaluation of vital signs		√	√	√	√	√	√	√	√	√	√	√	√	√
Medication administration history evaluation^‡^			√	√	√	√	√	√	√	√	√	√	√	√
Treatment	+ Acupotomy (combination treatment group)		√	√		√	√	√	√		√	√		
	NBT (all patients)				√					√				
Primary endpoint evaluation^§^		√					√					√	√	√
Secondary endpoint evaluation^||^		√					√					√	√	√
Exploratory efficacy evaluation^¶^													√	√^#^
Economic feasibility evaluation – cost evaluation^∗∗^		√					√					√	√	√
Adverse reaction monitoring			√	√	√	√	√	√	√	√	√	√	√	√
Economic feasibility evaluation – safety evaluation^††^			√	√	√	√	√	√	√	√	√	√	√	√

∗ One and 2 weeks are required from screening test to active treatment for combination treatment and NBT single treatment groups, respectively.

† Blood test [CBC 5 types, AST, ALT, ALP, albumin, BUN, protein, creatinine, total cholesterol, fasting glucose, RA, CRP, ASO, ESR, electrolyte 4 types (Na, K, Cl, T- CO_2_)]. It can replace test values performed within 8 weeks from screening.

‡ Concomitant medication history and adverse events monitoring are conducted at every visit for treatment and assessment.

§ ODI assessment.

|| Lower back and lower extremity pain (NRS) related to sacral neuropathy, quality of life (European Quality of Life 5 Dimension), Korean version of shortened MPQ, and Korean version of RMDQ.

¶ Additional NBT or surgical treatment within 4 weeks of the final procedure.

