**Efficacy evaluation**
In the efficacy evaluation, ITT will be treated as the main analysis group, and PP sets will be treated as the secondary analysis group. All statistical analysis will be conducted as two-sided tests with a significance level of 5%. Two-sided 95% confidence interval will be presented. Descriptive statistics will be presented for each treatment group and visit. Descriptive statistics and 95% confidence intervals will be presented for differences between the baseline and each visit.

Among efficacy evaluation variables, missing values of continuous variables will be analyzed using baseline observation carried forward correction.

A. Analysis of primary endpoints

For symptoms of lumbosacral radiculopathy at each measurement time point, descriptive statistics (number of patients, mean, and standard deviation) of the ODI score and changes in ODI at the end of treatment (4 weeks) and follow-up (8 weeks) compared with the baseline will be presented.

Paired *t*-test or Wilcoxon's signed ranked test will be conducted for intra-group changes in ODI at the end of treatment (week 4) compared with the baseline (0) depending on the satisfaction of normality. An analysis of variance model that includes changes in ODI at the end of treatment compared with the baseline as effects and baseline ODI as covariates will be used to evaluate the effects in the treatment group compared with the control group. Differences in least-square mean between treatment and control groups will be calculated, and two-sided 95% confidence interval and *P* value for the differences will be presented.

B. Analysis of secondary endpoint

Changes in ODI at follow-up (8 weeks) compared with baselineAssessment of subjective pain intensity in patients with lumbosacral radiculopathy-Lumbosacral radiculopathy pain will be divided into lower back and lower extremity pain using NRS, MPQ, and K-RMDQAssessment of quality of life related to lumbosacral radiculopathy-Evaluation of overall quality of life using EQ-5D. The same analysis methods for primary endpoints will be used to analyze secondary endpoints

C. Exploratory efficacy evaluation

Evaluation related to additional NBT or surgery after completion of the study

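### The early-termination rate is an odds rather than a proportion, and the additional-procedure rate has a numerator that its denominator does not fully cover (exploratory outcomes only)

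*Protocol article*

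**What the plan says.** Section 2.9, under the exploratory efficacy evaluation, prints two formulas, each multiplied by 100:

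- Early termination: "patients who completed the study early/patients who completed the entire study".
- Additional procedures: "patients who underwent additional procedures or surgeries/patients who completed the entire study".

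For the first it adds: "Chi-Squared test or Fisher exact test will be performed to compare the rate of early termination of treatment between the groups". For the second: "Chi-Squared test or Fisher's exact test will be performed to compare the rate of additional treatment and surgery between the groups".

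Section 2.8.3 sets out who is assessed for additional procedures. On early terminators: "This assessment will be not conducted on those whose symptoms have improved and ended the study earlier". On drop-outs: "For patients who dropped out in the middle of the study, the assessment will be performed at 4 weeks after dropout"; this may be done by telephone. A footnote to Table 1 repeats both rules.

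Section 2.8.7.2 says that early terminators are not counted as withdrawn and are regarded as compliant with treatment. The article does not define completion of the entire study.

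**The concern.** A rate compared by chi-squared or Fisher's exact test should be a proportion: every patient in the numerator is also in the denominator, and the rest of the denominator are the non-events. The early-termination formula contrasts finishing early with finishing the whole study, so its numerator appears to lie outside its denominator. The additional-procedure formula divides by completers, although the plan also collects the outcome in drop-outs and does not collect it in early terminators.

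Two things are at stake. The reported percentages could mislead, most of all in the arm with more early terminators. A test table formed by subtracting the numerator from the stated denominator could also show a difference that the counts do not support. In addition, completing the study is a post-randomisation event that treatment may affect, so dividing by completers compares groups selected differently in each arm.

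**Working it through.** **Inputs from the article.** Section 2.3 plans 20 patients per arm after 20% drop-out: 20 / (1 − 0.20) = 25 per arm, 50 in total. This reproduces the stated sample size. The article gives no expected early-termination or additional-procedure rate, so all event counts below are assumptions. Each arm has 25 randomised, 5 drop-outs and 20 others.

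**Are the two groups disjoint?** The formula itself sets early against entire. Section 2.8.7.2 describes these patients as finishing ahead of plan. Section 2.8.3 says they ended the study earlier. The missing-value rule for the economic evaluation groups them with withdrawn patients, as people with remaining visits to fill in. On the plain reading they are therefore not in the denominator.

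**Early-termination rate.** Let E be early terminators and F full completers, with E + F = 20. As written, the rate is 100 × E/F, which is the odds among patients who did not drop out. It exceeds 100% once E > F.

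| E | F | As written, E/F | E/(E+F) | E/25 randomised |
|---|---|---|---|---|
| 2 | 18 | 11.1% | 10% | 8% |
| 5 | 15 | 33.3% | 25% | 20% |
| 8 | 12 | 66.7% | 40% | 32% |
| 10 | 10 | 100% | 50% | 40% |
| 12 | 8 | 150% | 60% | 48% |

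**Effect on the test.** Assume 8 early terminators in the combination arm and 3 in control (F = 12 and 17). As written the rates are 8/12 = 66.7% and 3/17 = 17.6%, a gap of 49 points. Of those randomised they are 8/25 = 32% and 3/25 = 12%, a gap of 20 points.

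| Table (event, non-event; combination / control) | Chi-squared p, uncorrected | Fisher p |
|---|---|---|
| Stated denominator: 8, 12 − 8 = 4 / 3, 17 − 3 = 14 | 0.007 | 0.018 |
| Early vs full: 8, 12 / 3, 17 | 0.077 | 0.155 |
| Randomised: 8, 17 / 3, 22 | 0.088 | 0.171 |

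With 12 against 5 early terminators, the stated denominator gives a non-event cell of 8 − 12 = −4, so no test can be run. The early-versus-full counts (12, 8 / 5, 15) give chi-squared p = 0.025 and Fisher p = 0.054.

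**Additional-procedure rate, early terminators not counted as completers.** Assume 20 full completers, 4 with a procedure, and 5 drop-outs, 3 with a procedure. As written: (4 + 3)/20 = 35%. Completers only: 4/20 = 20%. All randomised: 7/25 = 28%. If no drop-out has a procedure, the formula gives 4/20 = 20%, a true proportion of completers.

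**Additional-procedure rate, early terminators counted as completers.** They enter the denominator but are never asked, so each is a non-event by construction. Assume the combination arm has 8 early and 12 full completers, 3 with a procedure, and control has 4 early and 16 full, 4 with a procedure; leave drop-outs aside. Among those assessed the arms are equal: 3/12 = 25% and 4/16 = 25%. The formula reports 3/20 = 15% and 4/20 = 20%, a difference created only by who was asked.

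**The case against.** The strongest defence is that early terminators count as completers. Section 2.8.7.2 treats them as compliant and not withdrawn, and the formula itself says they completed, only early. If the denominator means all completers, early or scheduled, the early-termination rate is a proper proportion. This reading is possible, but the section speaks of compliance with treatment, not completion of the study. It also moves the fault to the other rate, as the last calculation shows: patients never assessed become automatic non-events. No single meaning of completion makes both rates sound while Section 2.8.3 stands.

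Three further points limit the concern.

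- A reader might infer that both denominators miss their numerators. That is not so for additional procedures: full completers with a procedure are in both, and only assessed drop-outs can fall outside. The analysis heading, "Evaluation related to additional NBT or surgery after completion of the study", could even limit the numerator to completers. The rate would then be a proportion, but the drop-out assessment would feed no stated analysis.
- A reader might infer that the planned tests are invalid. They work on counts, not on the printed percentage. A test of early against full completers is arithmetically sound, although it conditions on not dropping out. Only a table built from the stated denominator fails.
- A reader might infer unequal observation windows from the Table 1 footnote, "Additional NBT or surgical treatment within 4 weeks of the final procedure", because the last planned procedure is at Day 21–22 in control and Day 26–28 in the combination arm. Sections 2.8.3 and 2.9 count from the end of treatment instead. The efficacy section sets that at 4 weeks for both arms, and Table 1 schedules the assessment at Day 56–58 in both. The wording differs and should be reconciled, but a difference between arms is not established.

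The Discussion mentions fewer surgeries as a possible benefit, but it does not tie that expectation to this formula.

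**Conclusion.** Wrong as written, for exploratory outcomes only. The early-termination formula gives an odds times 100. At the assumed counts it turns 32% of randomised patients into 67%, and 48% into 150%; the overstatement is small when early termination is rare (11.1% against 8% at 2 patients). The additional-procedure rate has a mismatch between those assessed and those counted in the denominator, not disjoint groups.

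The sizes rest on assumed event counts with 5 drop-outs per arm, and on the plain reading of who completed the entire study. The primary ODI analysis uses neither rate and is unaffected.

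**What to change.** 1. For both rates, use all patients randomised to the arm as the denominator. The article's ITT set would also give a proportion for early termination, but it drops patients without a follow-up, so all randomised is the cleaner choice.
2. Build the chi-squared or Fisher tables from those counts: patients with the event, and the remaining randomised patients. Report separately anyone whose procedure status could not be obtained.
3. Ask early terminators as well as drop-outs about further NBT or surgery up to the Day 56–58 visit, using the telephone route that Section 2.8.3 already allows for drop-outs.
4. Reconcile the Table 1 footnote with Sections 2.8.3 and 2.9 on the point from which the 4 weeks are counted.

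The cost is two reworded formulas, an aligned footnote, a short call to each early terminator, and a later time point for the call already planned to drop-outs. Sample size and the primary analysis do not change.
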